**Figure 2 F2:**
[figure not shown]
The screenshot for the portable electrical equipment and the *Xinankang* app for patients (English version). Instructions on how to wear a close-fitting the portable electrical equipment and rehabilitation record details including metabolic equivalent, heart rate and exercise prescription, etc.

Rehabilitation physicians review patients' health data during home exercise training, and provide suggestions. If the patient's condition worsens, the system can be used to coordinate a referral to the hospital. We applied the *Xinankang* app to integrate patients, home electrical equipment, and doctors. Adherence is assessed during telephone calls and review of the participant's exercise diary.

### Cardiac Magnetic Resonance Imaging Procedure

CMR imaging is performed on a clinical Philips system (3.0 T, Philips Healthcare, Best, The Netherlands) with simultaneous ECG recording (21). RV wall thickness, stroke volume (SV), RV and left ventricle (LV) ejection fractions are obtained (21). RV/LV masses and end-diastolic volumes were obtained from the endo- and epicardial contours of the RV and LV delineated manually by blinded observers. The detailed CMR images, layers and sequences of above-mentioned parameters were available on Supplementary Material 3.

### Outcomes

#### Primary Efficacy Outcome

The changes of right ventricular stroke volume (RVSV) from baseline to Week 26 are determined by CMR. RVSV indexed for BSA is shown to predict outcome (22). RVSV quantifies blood flow independently of HR. An increase in RVSV reflects favorable, reverse remodeling of the right ventricle (RV) and is expected to reduce PAH symptoms through better oxygenation.

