## Abstract

**Background:**

Patients with pulmonary arterial hypertension (PAH) have reduced exercise capacity and poor quality of life. Exercise-based rehabilitation in PAH results in clinically relevant improvements in exercise capacity and hemodynamics. To clarify the mechanism, we will evaluate the effect of aerobic exercise training rehabilitation on right ventricular (RV) remodeling and function as determined measured by cardiac magnetic resonance imaging (CMR).

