## Introduction

Pulmonary arterial hypertension (PAH) is characterized by progressive remodeling of the pulmonary vasculature, which results in limited exercise capacity, progressive increase in breathlessness and right ventricular remodeling, and eventual death (1). Advances in PAH-targeted medications have significantly improved prognosis, and other therapies need to be further explored in order to improve exercise capacity and quality of life (QoL) (2). There is strong evidence that exercise training improves cardiorespiratory fitness, functional status, and clinical outcomes of patients with other heart or lung diseases (3, 4). There was a time when PAH patients were actively discouraged from exercise rehabilitation because of fear of exercise risk. However, exercise training has recently shown beneficial effects as add-on to PAH-targeted treatment in different etiologies of pulmonary hypertension (PH), such as IPAH (3, 5–8), inoperable chronic thromboembolic PH (CTEPH) (4), and associated PAH in connective tissue diseases (9).

Supervised rehabilitation, including exercise training have been proved to improve pulmonary hemodynamics, exercise capacity, QoL, and possibly RV function in patients with PH (Class I, A) (5–15). Currently, most exercise training trials published have focused on exercise capacity of patients with PH. The European Respiratory Society statement on exercise training and rehabilitation acknowledges that gaps in knowledge exist (15). Among them, the mechanisms of improved exercise capacity and hemodynamics by exercise training in PAH remain incompletely understood.

Increased cardiac output may be explained by a decreased RV afterload and direct training effect on heart. Therefore, further research on the effects of exercise training in PAH should consider the endpoints of RV properties.

Cardiac magnetic resonance imaging (CMR) is the gold standard for non-invasive assessment of RV function. Images of slices in any plane can be obtained with a very good spatial and temporal resolution. This translates into a low variability of inter-study and inter-rater CMR assessments which allows a reduced sample size for clinical trials compared to other imaging tools (16).

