#### Secondary Efficacy Outcome

In the same method as that used for the primary endpoints, secondary endpoints are assessed at 26 weeks. They consist of characteristics of the RV, and of widely accepted tools to assess PAH progression:

RV end diastolic volume (RVEDV),RV end systolic volume (RVESV),RV ejection fraction (RVEF),RV mass,WHO FC,6 MWD, andN-terminal pro-B-type Natriuretic peptide (NT-proBNP).

Variables pertaining to the left ventricle (LV) are also assessed.

Changes from baseline to Week 26 in:

LV SV,LV end diastolic volume (LVEDV),LV end systolic volume (LVESV),LV ejection fraction (LVEF),LV mass,RVEDV/LVEDV, andRVESV/LVESV.

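### A rise in RVSV is read as heart-rate-independent flow and as reverse remodelling, but RVSV is a volume per beat and no listed endpoint separates more flow from a slower heart

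*Protocol article*

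**What the plan says.** The primary endpoint is defined in the Primary Efficacy Outcome section: "The changes of right ventricular stroke volume (RVSV) from baseline to Week 26 are determined by CMR". Two interpretive statements follow, the first about flow and the second about structure: "RVSV quantifies blood flow independently of HR. An increase in RVSV reflects favorable, reverse remodeling of the right ventricle (RV"). Neither carries a condition on heart rate or on RV volumes.

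The Secondary Efficacy Outcome section lists "RV end diastolic volume (RVEDV),RV end systolic volume (RVESV),RV ejection fraction (RVEF),RV mass,WHO FC,6 MWD" and NT-proBNP, then LV stroke volume, LV volumes, LVEF, LV mass and two RV/LV volume ratios. The exploratory endpoints are omics. Cardiac output, cardiac index and HR are in none of these lists. Table 2 ticks right heart catheterisation at screening only. The primary ANCOVA described under Statistical Analysis has baseline RVSV as covariate and other PAH therapy as a factor.

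The scan is performed "with simultaneous ECG recording", so HR during imaging is available, although the article does not name it as an output.

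**The concern.** A per-beat volume does not measure flow unless it is multiplied by the beat rate. If training slows the resting heart and flow stays the same, RVSV rises. Randomisation does not protect against this, because the slower heart would be an effect of the intervention and not a chance imbalance. LV stroke volume, the nearest listed companion, is also per beat and would move the same way.

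The remodelling statement has a similar weakness. RVSV is RVEDV minus RVESV, so it rises when the ventricle empties better and also when it enlarges. Only the first is reverse remodelling.

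At stake is what a positive primary result may be said to show. The abstract sets a mechanistic purpose: "To clarify the mechanism, we will evaluate the effect of aerobic exercise training rehabilitation on right ventricular (RV) remodeling and function". If the two statements stand, a significant RVSV difference could be reported as better flow and reverse remodelling without the evidence that separates these from the alternatives.

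**Working it through.** The article gives no HR or cardiac output figure, so there is no figure of the plan's own to reproduce here. The sample-size numbers do not enter this point, except the effect of about 9 mL used as a yardstick.

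**Inputs**
- Starting RVSV 52.2 mL, change of about 9 mL, clinically relevant range 8 to 12 mL: Sample Size Calculation.
- Resting HR: not given; assumed 70 to 85/min.
- Fall in resting HR: not given; 5 and 10 beats used as illustrations.
- Flow: held constant by assumption, to isolate the HR route.
- RVEF: not given; assumed 35% to 45%.

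**Step 1: slower heart, same flow.** Cardiac output = SV × HR. With output fixed and a fall of d beats, new SV = 52.2 × HR / (HR − d).

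| Assumed HR | 5-beat fall | 10-beat fall | Fall giving +9 mL |
|---|---|---|---|
| 70 | 52.2 × 70/65 = 56.2 (+4.0) | 52.2 × 70/60 = 60.9 (+8.7) | 10.3 |
| 75 | 52.2 × 75/70 = 55.9 (+3.7) | 52.2 × 75/65 = 60.2 (+8.0) | 11.0 |
| 80 | 52.2 × 80/75 = 55.7 (+3.5) | 52.2 × 80/70 = 59.7 (+7.5) | 11.8 |
| 85 | 52.2 × 85/80 = 55.5 (+3.3) | 52.2 × 85/75 = 59.2 (+7.0) | 12.5 |

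The last column is HR × 9 / (52.2 + 9) = HR × 0.147.

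**Step 2: larger ventricle.** RVSV = RVEDV − RVESV = RVEDV × RVEF.
- RVEF unchanged: a 9 mL rise in RVSV needs RVEDV to rise by 9/RVEF, which is 9/0.45 = 20.0 mL to 9/0.35 = 25.7 mL. RVESV then rises by 11.0 to 16.7 mL. That is dilatation.
- RVESV unchanged: a 9 mL rise in RVEDV gives the same 9 mL in RVSV. At an assumed RVEF of 40%, RVEDV goes from 52.2/0.40 = 130.5 to 139.5 mL, and RVEF goes to 61.2/139.5 = 43.9%. RVEF improves although the ventricle is larger, so RVEF alone would not expose this pattern. RVEDV would.

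**Step 3: what the listed endpoints can show.**
- Larger ventricle: visible in RVEDV and, depending on the pattern, in RVESV, RVEF and RV mass.
- Slower heart at constant flow: not identifiable, because every listed ventricular measure is a volume, a mass or a ratio of volumes. None contains time or rate.

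**The case against.** Several counter-arguments have force.

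- *Dilatation is already covered.* This stands. RVEDV, RVESV, RVEF and RV mass are secondary endpoints at 26 weeks. A reader might infer that RV enlargement would pass unnoticed as a favourable result; the endpoint list does not support that. What remains is that the sentence on remodelling makes a rise in RVSV sufficient by itself.
- *The trial does not set out to explain cardiac output.* This also stands. The Introduction contains "Increased cardiac output may be explained by a decreased RV afterload and direct training effect on heart", but as background. The aim stated at its end is the effect of training on RV properties by CMR. A reader might infer that the trial cannot answer its own question; that goes too far.
- *The HR route is hypothetical.* No resting HR or training effect on it is given. The HR in Table 1 sets exercise intensity and says nothing about resting rate. The Discussion cites one invasive randomised study in which resting cardiac index rose, which points away from constant flow. The programme lasts 2 + 10 = 12 weeks and the endpoint is at Week 26, so any fall in HR would have to persist for 14 weeks after the prescribed training ends. The route is therefore possible, but its size is unknown.
- *The HR phrase may only mean that HR is not a component of the measure.* That reading is fair, but it is the very reason why RVSV alone cannot quantify flow.
- *Cardiac output could be derived anyway.* It could, from the ECG at the scan. But no such analysis is named, and the vital signs in Table 2 belong to a Week 16 column, not to a Week 26 scan.

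**Conclusion.** The point holds as one of interpretation. The two statements claim more than RVSV can show, and the HR alternative is not addressed by any listed endpoint. The dilatation alternative is addressed by the secondary endpoints, but the stated reading is not linked to them.

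The illustrative size is 3.3 to 4.0 mL for a 5-beat fall (36% to 45% of 9 mL) and 7.0 to 8.7 mL for a 10-beat fall (77% to 97%). It rests on an assumed HR of 70 to 85/min, assumed falls and constant flow. It should not be read as an estimate of bias, nor as a prediction that a positive result would be due to a slower heart; the documents support neither. RVSV remains a legitimate primary endpoint, and its test and type I error are unaffected.

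**What to change.** 1. Keep RVSV as the primary endpoint.
2. In the Primary Efficacy Outcome section, delete the claim of independence from HR and replace the unconditional remodelling statement with one that refers to the RV volumes.
3. In the Secondary Efficacy Outcome section, add CMR cardiac output or index (SV × HR from the ECG already recorded at the scan) and HR at the scan as supportive endpoints. Say which ventricle's stroke volume is used, since both are measured.
4. State the reading in advance, in terms of between-group differences. Improved flow is concluded only if CMR cardiac output also rises. Reverse remodelling is concluded only if RVESV falls and RVEDV does not rise, with RVEF in agreement. Given a rise in RVSV, the RVEDV condition is the one that binds: if RVEDV does not rise, RVESV must fall and RVEF must rise by arithmetic, so those two serve as consistency checks.
5. Do not add follow-up HR as a covariate in the primary ANCOVA. It is measured after randomisation and may be affected by training.

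The cost is wording and a few derived variables from scans already planned, with no extra procedure. The downside is that a positive RVSV result may support a narrower claim.

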#### Secondary Efficacy Outcome

In the same method as that used for the primary endpoints, secondary endpoints are assessed at 26 weeks. They consist of characteristics of the RV, and of widely accepted tools to assess PAH progression:

RV end diastolic volume (RVEDV),RV end systolic volume (RVESV),RV ejection fraction (RVEF),RV mass,WHO FC,6 MWD, andN-terminal pro-B-type Natriuretic peptide (NT-proBNP).

Variables pertaining to the left ventricle (LV) are also assessed.

Changes from baseline to Week 26 in:

LV SV,LV end diastolic volume (LVEDV),LV end systolic volume (LVESV),LV ejection fraction (LVEF),LV mass,RVEDV/LVEDV, andRVESV/LVESV.

#### Exploratory Efficacy Outcome

The following exploratory endpoints aim to investigate the molecular impact of exercise training on patients, including metabolomic, lipomic, and proteomic changes from baseline to Week 26 for subjects who agreed to participate in optional proteomic, metabolomic, and transcriptomic analysis, blood samples are collected at baseline and Week 26. The effects of rehabilitation exercise on proteomics, metabolomics, and transcriptomics in patients with PAH are observed. Subjects can agree to participate in all, part, or none of these analyses, and subjects who are unwilling to participate can still participate in the main clinical study.

### Study Timeline

A diagram timeline is presented in Table 2. Elaborated baseline evaluations are shown in Supplementary Material 3.

**Table 2 T2:** Study timelines overview.

	**Screening**	**Baseline**	**Observation period**		
	****~**0 month**	**0 month**	**Week 12**	**Week 16**	**Preterm termination**
On-site clinic visit		**√**			**√**
Monthly telephone contact			**√**	**√**	**–**
Informed consent	**√**	**–**	**–**	**–**	**–**
Review eligibility criteria	**√**	**√**	**–**	**–**	**√**
Demographics	**√**	**√**	**–**	**–**	**√**
PAH history	**√**	**√**	**–**	**–**	**–**
Medical history	**√**	**√**	**–**	**√**	**√**
Body mass index	**√**	**–**	**–**	**√**	**√**
Physical examination	**√**	**√**	**–**	**√**	**√**
Vital signs	**√**	**√**	**–**	**√**	**√**
6MWD/HHR	**√**	**√**	**–**	**√**	**√**
Borg scores	**√**	**√**	**–**	**√**	**√**
Echocardiography	**√**	**√**	**–**	**√**	**√**
Right heart catherization	**√**				
Pulmonary function test	**√**				
V/Q lung scan	**√**				
CPET	**√**	**√**	**–**	**√**	**√**
WHO functional class	**√**	**√**	**–**	**√**	**√**
Electrocardiogram	**√**	**√**	**–**	**√**	**√**
Chemistry, hematology		**√**		**√**	
NT-proBNP	**–**	**√**		**√**	
Randomization	**√**	**√**	**–**	**–**	**–**
AE monitoring	**√**	**√**	**–**	**√**	**√**
Concomitant medication	**√**	**√**	**–**	**√**	**√**
Omics*	**√**			**√**	**√**

*6MWD, 6-min walk distance; NT-proBNP, N-terminal pro-brain natriuretic peptide; PAH, pulmonary arterial hypertension; V/Q, ventilation-perfusion; WHO, World Health Organization; CPET, cardiopulmonary exercise testing; HHR, heart rate recovery; AE, adverse event. *Omics indicates proteomics, metabolomics and transcriptomics*.

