## Methods And Analysis

### Study Design and Setting

The study of the efficacy and safety of aerobic exercise training in PAH (the Saturday study) will recruit subjects from 1 June 2020 to 1 June 2023. The study is a 26-week multicenter, prospective, and RCT. Subjects willing to consider enrollment will be consented. Patients with PAH stable on PAH-targeted drugs for at least 3 months prior to inclusion are randomly assigned to the control and training groups. Medication remains unchanged during the study period (Figure 1). We will use the SPIRIT checklist and TIDiER checklist when writing our report (Supplementary Materials 1, 2) (17, 18). All centers will follow a standardized protocol, including rehabilitation, diagnosis, and evaluation of PAH, as shown in Table 1.

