### Rehabilitation Program With Aerobic Exercise Training

Exercise training is started in-the hospital for 2 weeks. Patients spend 30 min per session 3 days/week. A cardiopulmonary exercise test prior to enrolment was performed to determine the anaerobic threshold (AT). We perform interval cycle ergometer training at workloads of 1 min before the AT. The training intensity was adjusted by oxygen saturation (SaO_2_), heart rate (HR), and blood pressure monitored throughout the training. Patient receive oxygen supply throughout the training when SaO_2_ falls below 90% during exercise. Patients who were on daily oxygen before enrollment remain on oxygen. The exercise training includes two aerobic exercise training sessions, namely, 2-week supervised exercise training in the hospital and 10-week training at home. The home-based program is walking with exercise intensity at an AT of 30 min/day for 3 days a week for 10 weeks. Detailed FITT principle is shown in Table 1. In our study protocol, we choose AT intensity because AT intensity stands for aerobic exercise, which can avoid the accumulation of lactic acid in the body, avoid excessive activation of sympathetic nerve, excessive myocardial oxygen consumption, or arrhythmia. The AT intensity is expressed by the HR or the number of steps (the speed of the AT divided by the step distance). Patients in this group at home are managed by the *Xinankang* home electrical equipment system together with PAH experts, physiatrists, and physiotherapists. The home system consists of the portable electrical equipment and *the Xinankang* app for patients to upload their health data, and communicate with the *Xinankang* app uploaded by physiatrists and physiotherapists. This app also reminds participants to complete their training and follow-up on time (Figure 2).

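### Table 2 schedules no adverse-event or concomitant-medication collection after baseline until after the 12-week training period, although a telephone contact is ticked at Week 12

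*Protocol article*

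**What the plan says.** The Study Design and Setting section presents the trial as "The study of the efficacy and safety of aerobic exercise training in PAH" and requires medication to stay the same throughout. The Statistical Analysis section provides a separate population for the safety analysis.

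The Rehabilitation Program section describes "2-week supervised exercise training in the hospital and 10-week training at home". In hospital, oxygen saturation, heart rate and blood pressure are watched during sessions. For the home phase it says "Patients in this group at home are managed by the" app-and-device system, and the text after Figure 2 adds "Rehabilitation physicians review patients' health data during home exercise training, and provide suggestions". No comparable arrangement is described for controls.

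Table 2 is the only schedule shown. Its rows "AE monitoring" and "Concomitant medication" are ticked at screening, baseline, Week 16 and preterm termination, and dashed at Week 12. The row "Monthly telephone contact" is ticked at Weeks 12 and 16 and is not split by arm.

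The Adverse Events section sends every serious event to the principal investigator. It has other events recorded and followed up, with no limit by visit or arm. It does not say when or how participants are asked.

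**The concern.** Exercise-related harm is most likely to arise in the weeks when patients are training, and these are the weeks with no scheduled question about adverse events. What is learned then must come from spontaneous reports or from the extra contact that training itself brings, and only one arm has that contact. Patients know their allocation. If minor events come to light through sessions and app review in one arm and depend on later recall in the other, the arms are not compared on the same footing. The likely direction would be to make training look less safe than it is.

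Concomitant medication raises a separate issue. The design depends on medication not changing, and this row is the scheduled check on that. A change made during training would have no scheduled record until the next ticked column.

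**Working it through.** The document gives no adverse-event rate and no figure on this point, so there is nothing to reproduce. The check sets the schedule beside the text and counts weeks.

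**1. The rows in Table 2**

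| Row | Screening | Baseline | Week 12 | Week 16 | Preterm termination |
|---|---|---|---|---|---|
| Adverse events | tick | tick | dash | tick | tick |
| Concomitant medication | tick | tick | dash | tick | tick |
| Telephone contact | blank | blank | tick | tick | dash |

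The Week 12 entries are explicit dashes. The same table leaves other cells empty (NT-proBNP at Week 12, for example), so these are entries and not gaps.

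**2. Length of training** (Table 1 and the Rehabilitation Program section)

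2 weeks in hospital + 10 weeks at home = 12 weeks. Week 12 is the end of training.

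**3. Ticked collections after baseline and up to Week 12**

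There are none for either row in either arm, unless a patient terminates early.

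**4. Interval to the next ticked collection**

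- As labelled: 16 − 0 = 16 weeks from baseline, and 16 − 12 = 4 weeks after training ends.
- If the column stands for Week 26 (an assumption): 26 − 0 = 26 weeks from baseline, and 26 − 12 = 14 weeks after training ends.

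The second reading is plausible. The Outcomes section places NT-proBNP, walking distance, functional class and the omics samples at Week 26, Table 2 has no Week 26 column, and these assessments appear under Week 16. Either way, no ticked collection falls within training.

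**5. Other channels in Weeks 1 to 12**

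- Training arm: 3 sessions × 2 weeks = 6 monitored hospital sessions, then 3 × 10 = 30 home sessions with the app, the device and physician review.
- Control arm: no such channel is described. The telephone row applies to both arms, but the only use the text gives for the calls is checking adherence, and Table 2 ticks nothing else in the Week 12 column.

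**6. Schedule against text**

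The Adverse Events section implies continuous recording without fixing when participants are asked. Table 2 fixes the asking and marks it absent at the one column that falls at the end of training. The two do not give one clear rule.

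**The case against.** The strongest reply is that the Adverse Events section has both serious and other events recorded with no restriction to visits or to one arm. A dash in an overview table does not override that. This stands: a reader might infer from Table 2 that collection stops during training, and the document does not show this. It shows a schedule and a general rule that have not been reconciled.

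Three further replies have force.

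- The telephone row is called monthly and is not arm-specific, so controls may well be called during training, and an article can leave the content of calls to the full protocol. But the dashes are stated entries and not missing detail, and they say that these two items are not collected at a call.
- A reader might infer that training-period harms are detected late in general. That does not fit the training arm, which is supervised for 2 weeks and then reviewed through the app. Delay is more plausible for control-arm events and for medication changes.
- A reader might infer that the adverse-event comparison is biased against training. Nothing says that app data enter the adverse-event record, and Table 2 applies the same dashes to both arms. Unequal ascertainment is a risk, not an established fact.

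It can also be said that no adverse-event endpoint is listed and that closer observation of people who exercise under supervision is inherent in such a trial. Both are fair and limit the weight of the point. Neither explains why a call already planned should not ask about adverse events.

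**Conclusion.** The point holds as a cheap improvement. As written, Table 2 has zero ticked post-baseline collections of adverse events or concomitant medication during or at the end of the 12-week training period. The next is 16 weeks after baseline as labelled, or 26 weeks if the column is a misprint for the final assessment. This needs to be reconciled with the Adverse Events section, the safety aim and the unchanged-medication condition.

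The consequence for the between-arm comparison is a risk of fuller ascertainment in the training arm. It rests on two assumptions: that sessions and app review bring events to light, and that controls have no equivalent prompt. Its size is unknown. The document gives no event rates and no reporting fractions, so any rate ratio put on it would only restate whatever fractions were assumed.

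**What to change.** Reconcile Table 2 with the Adverse Events section as follows.

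- Tick the adverse-event and concomitant-medication rows at every monthly telephone contact, including Week 12, and at the final Week 26 assessment. If monthly means every four weeks (an assumption), the calls fall at Weeks 4, 8, 12, 16, 20 and 24. With Week 26 that makes 7 post-baseline collections, of which 3 are within or at the end of training.
- Ask the same questions in both arms.
- Base the between-arm adverse-event comparison on these common contacts, and list separately any events found only through the app or supervised sessions.
- State whether the column labelled Week 16 is a separate contact or the Week 26 assessment.

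The cost is a few minutes per call on calls the plan already describes as monthly, a case report form page, and more adverse-event records to process.
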